## Abstract

**Background:** Staff nurses face frequent emotional situations in their work environment. The constant contact with suffering patients, and the busy work environment, pose tremendous stress on nurses’ physical and emotional health. The Emotional Intelligence skills of empathy, self-awareness, motivation, self-control, and keeping relationships, can help handle difficult emotions and allow nurses to work in an organized, calm, and professional way.

This study aims to implement and assess the effectiveness of a training program developed by the investigator, tailored to the mental and emotional needs of staff nurses who are working in an organization. The study also aims to observe any significant change, correlation, and association in the staff nurses’ level of emotional intelligence, intrinsic motivation, self-compassion, emotional labor, and nurse-in-charges’ and patients’ perception of nursing care after the program.

**Methods:** A quasi-experimental (one-group) study design was used in this study. The study will involve 80 staff nurses working in a selected hospital in India. The staff nurses will be selected from the hospital’s general wards using convenience sampling. For the current study, a quasi-experimental design will be used. The investigator will deliver a training program, divided into four sessions of two hours each. Data will be collected from the participants at baseline and 3-months pre-intervention; and post-test data will be collected immediately after the intervention, at 3-month, and 6-month follow-up, to observe any significant change in the study variables before and after the intervention.

**Results:** The current study primarily focuses on the vital aspect of developing emotional needs, for promoting a better work-life balance. Research findings from the study will significantly contribute to the evidence based Emotional Intelligence programs for staff nurses, and if proven effective, could be delivered extensively in the hospitals.

**Trial registration:** The study is registered in June 2019 under the Central Trial Registry of India (
CTRI/2019/08/020592).

## Introduction

1.

Nurses are faced with frequent emotional situations in their work environment which may hinder their decision-making, concentration, and recall, and may lead to an increase in errors. Thus, the skills of emotion regulation may help them in handling difficult emotions, especially in the times of crisis, and allow them to act appropriately.

### Background

1.1

Emotion is a complex feeling that results in physical and psychological changes which influence thoughts and behaviours (
Drigas & Papoutsi, 2018), motivate our decisions (
Keltner & Kring, 1998), and guide our interpersonal relationships (
Susskind, Lee, Cusi, Feiman, Grabski, & Anderson, 2008). Emotions are fundamental to nursing practice and play a vital role in the interaction with colleagues and patients. It is through the exchange and perception of emotions that nurses and patients initiate, establish, and maintain a therapeutic relationship. Therefore, it is essential that nurses understand and manage their own emotions and are skilled in managing others’ emotions.

Nurses face various difficult events and emotions due to the nature of the job itself, which puts them in a vulnerable position (
Lee, 2019). Additionally, nurses are expected to control their emotional reactions while calming their patients’ distress, show empathy, be always amiable (
Ryan & Deci, 2000), express positive emotions, and suppress negative emotions (
Glomb & Tews, 2004). Such experiences can be overwhelming, emotionally laborious, and expose nurses to “psychological strain” (
Zaghini, Fiorini, Piredda, Fida, & Sili, 2020). When nurses experience such tremendous occupational stress, the motivation to engage in work and serve others lowers, potentially leading to a loss in productivity (
Jiang, Jia, Zhang, Li, Song, & Yu, 2021) and ultimately negatively affecting their quality of care (
Varghese, George, Kondaguli, Naser, Khakha, & Chatterji, 2021).

In recent years, various emotional well-being components/concepts have garnered the attention of scientists and have been proven to impact a variety of outcomes in healthcare workers such as optimal physical and psychological health, intelligent decision-making, effectively managing workload, burnout and stress (
Hotchkiss, 2018), as well as improved ability to care for patients with greater compassion and more sustainably, sensitivity, and empathy and improved interpersonal skills (
Søvold, Naslund, Kousoulis, Saxena, Qorondleh, Grobler, & Münter, 2021). One such concept is Emotional Intelligence (EI) which can be defined as an individual’s ability to understand others and their own emotions to make intelligent decisions. Previous studies have suggested that individuals with high EI have a set of emotional aptitudes and competencies that enable them to evaluate and regulate their as well as other’s emotions (e.g., anger) to reach a variety of adaptive outcomes or emotional states (e.g., motivation) (
O’Connor, Hill, Kaya & Martin, 2019). The available literature in Nursing also recognizes EI as a crucial element in providing patient-centred care (
Giménez-Espert & Prado-Gascó, 2018), and suggests that nurses with higher EI experiences less professional stress, perform better at work, have better communication skills, are empathetic and solves problems more effectively (
Kahraman & Hicdurmaz, 2016). These findings emphasize the importance of EI in nursing.

Intrinsic motivation (IM), self-compassion (SC) and emotional labour (EL) have also been closely linked with EI in the available literature. Nurses with higher emotional regulation skills were found to have high IM (
Lelorain, Bachelet, Goncalves, Wortel, Billes, Seillier, Bertin, & Bourgoin, 2018). This suggests that interventions aiming at improving nurses’ emotional regulation/EI skills may also improve their IM.

Kristen Neff (2003) defined SC as being open to and moved by one’s suffering, experiencing feelings of caring and kindness toward oneself, taking an understanding non-judgmental attitude toward one’s inadequacies and failures and recognizing that one’s own experience is part of the common human experience.
Neff (2003) also suggests that individuals who are capable of self-compassion are kind to themselves and accept reality, and in doing so hold a balanced awareness of their thoughts and feelings by being emotionally intelligent. Within the nursing literature SC is found to be positively associated with higher EI (
Heffernan, Griffin, McNulty, & Fitzpatrick, 2010;
Kousar, Kousar, Afzal, Waqasr, & Gilani, 2017;
Joseph & Elias, 2019), higher IM (
Kotera, Taylor, Fido, Williams, & Tsuda-McCaie, 2021), greater well-being (
Durkin & Beaumont, 2016), lower compassion fatigue and burnout (
Beaumont, Irons, Rayner, & Dagnall, 2016;
Dev, Fernando, Lim, Consedine, 2018;
Durkin & Beaumont, 2016).

As mentioned earlier, nurses are always in direct contact with patients who are suffering. In this interaction, nurses are always expected to keep a check on their as well as patients’ emotions. Pam Smith defined this as emotional labour, which is the act or skills that are involved in caring for and recognizing the emotions of others and not only the emotions experienced by nurses (
Freitas, Costa, Diogo, & Gaiva, 2021). Available literature indicates that nurses experience mild to moderate EL, which if remains unchecked, leads to emotional dissonance, emotional exhaustion (
Badolamenti, Sili, Caruso, & Fida, 2017), stress and burnout (
Delgado, Upton, Ranse, Furness, & Foster, 2017). However, EL is also recognized as an essential characteristic of nurse-patient interaction (
Delgado, Upton, Ranse, Furness, & Foster, 2017), and the caring process (
Tuna & Baykal, 2017) which helps nurses in establishing and maintaining a trusting relationship with patients (
Yeh, Chen, Yuan, Chou, & Wan, 2020).

Despite the obvious emotional element of nurses’ work, there remains a dearth of professional acknowledgement and literature on emotional work in nursing practice (
Williams, 2013). After performing a thorough literature search, the investigator identified a few research gaps. First, very few studies in the available literature have implemented and tested interventions designed to enhance nurses’ emotional intelligence, intrinsic motivation, self-compassion, and emotional labour. Second, studies that have assessed the effectiveness of an intervention to improve nurses’ EI, IM, SC and EL for a longer follow-up are very minimal. Third, limited studies have explored the relationship between nurses’ EI, IM, SC, and EL. Fourth, although there is enough evidence indicating that nurses’ ability to regulate emotions influences the quality of care (
Khademi, Abdi, Saeidi, Piri, & Mohammadian, 2021), no previous studies have assessed the perception of nursing care after the nurses underwent emotional-wellbeing training. It was also observed that studies on patients’ perception of nursing care are inadequately explored in low-income countries (
Gishu, Weldersadik, & Tekleab, 2019;
Kewi, Tasema, & Negussie, 2018;
Dikmen & Yilmaz, 2017), as well as no studies were found that assessed nurse-in-charges’/supervisors’ perception of nursing care.

Recent studies suggest that more than 87.6% of nurses in India experience stress in their workplace (
Bai & Ravindran, 2020). Factors such as work overload, poor staffing, long shift hours, dealing with death and suffering, and rapidly changing technology, lead to increased fatigue, low motivation, increased error (
Wu, Zhu, Wang, Wang, & Lan, 2007), excessive anger and worry (
Kane, 2009), anxiety and depression (
Chaudhury, Mazumdar, & Mehta, 2018). In 2015, the United Nations (UN) Sustainable Development Goals (SDG) defined mental health as a priority for global development for the next 15 years. As the patient population is increasing, with ever-increasing stressors for nurses, it is a need of the moment that mental health and emotional wellness are paid due consideration and are strengthened (
WHO, 2022) by using both general and targeted evidenced-based interventions, and by creating and promoting strength-based intervention and preventative programs. Remarkably, studies that focus on improving positive emotions, motivation and behaviors of healthcare workers are rare (
vanDorssen-Boog, vanVuuren, DeJong, & Veld, 2021). As EI, IM, SC (
Fabio & Saklofske, 2021) and EL are among the many identified primary prevention resources, linked with psychological health and well-being in previous research, interventions aimed at supporting and strengthening nurses’ personal and psychological resources would not only aid in enhancing their emotional regulation, emotional well-being, and coping mechanisms, but they may also improve patient care. The investigator of this study has weaved these components of emotional well-being together with the purpose to strengthen them through a training program for promoting a better work-life balance.

### AIM

1.2

This study’s primary aim was to develop, validate, and implement a structured Integrated Emotional-Self Enhancement (IESE) Program among staff nurses and examine the program’s impact on the staff nurses’ EI, IM, SC and EL, as well as on the patients’ and nurse-in-charges’ perception of nursing care.

## Methods

2.

### Trial registration

2.1

The study is registered in June 2019 under the Central Trial Registry of India (
CTRI/2019/08/020592).

### Design

2.2

The current study has a quasi-experimental (one-group) design, which involves staff nurses working in the general wards of a selected hospital. The present study’s design is well suited, keeping in mind the work shifts of staff nurses and the number of staff nurses in the selected hospital. To derive a better understanding of whether intervention on emotional well-being components would affect staff nurses and the perception of patients and nurse-in-charges, the current study has based its concept on Neuman’s System Model and King’s Interacting Systems Theory to design the conceptual framework. Both of these theories have been proven effective in providing guidance for applying the theoretical understanding to practical clinical nursing situations to improve practice (
Montano, 2021;
Shanta & Connoly, 2013).

### Study site

2.3

The study will be conducted in a selected tertiary care hospital in Mangalore, India. This multispecialty hospital has outpatient and inpatient facilities that cater to patient care, teaching, and scientific research. The hospital has approximately a total of 450 staff nurses. The staff nurses have three shift duty hours viz. morning, evening, and night shifts. To maintain the confidentiality of the study participants, the hospital name is not disclosed.

### Study participants

2.4

The staff nurses working in the selected hospital’s general wards, who match the inclusion and exclusion criteria, will be considered as a potential study participant. All the nurses who provide their consent to participate will be considered for recruitment in the study. However, only those who fulfill the inclusion criteria will be included for the final sample. The IESE program will be delivered to all the recruited staff nurses. Also, data about the perception of nursing care will be collected from the patients who are under the direct care of the recruited nurse participants, and from the nurse-in-charges who are supervising the recruited nurses. The program will not be provided to the patients and nurse-in-charges.
Table 1 shows the summary of the inclusion and exclusion criteria of study participants. The confounding factors will be controlled by applying an appropriate research design, communicating clearly with the participants and stakeholders, and by making the duty roster of staff nurses well in advance.

**Table 1. T1:** Summary of inclusion and exclusion criteria.

	Nurse	Nurse-in-charge	Patient
**Inclusion criteria**	Staff nurses working in a selected hospital at Mangalore, Karnataka, India.	Nurse-in-charge working in a selected hospital at Mangalore, Karnataka, India.	Patients who are willing to participate.
	Staff nurses who are willing to participate in the study.	Nurse-in-charge who are willing to participate in the study.	Patients in the age group of 18-60-years.
			Patients who can read Kannada and English.
			Patients who are conscious.
**Exclusion criteria**	Staff nurses with earlier exposure to similar programs.	Nurse-in-charge working in psychiatric units, Out-patient-department, and Intensive Care Units.	Patients with current diagnosis of mental illness.
			Patients who are critically ill.
	Staff nurses working in psychiatric units, Intensive Care Units, and Out-patient Departments.		Patients who are admitted for less than 3 days.

### Sample size and selection

2.5

For the current study, all staff nurses working in the general wards will have the probability of being selected. At a 20% dropout rate, 80% power, SD of 12.3 (taken after feasibility study), and clinically significant difference of 5, it was calculated that approximately 63 staff nurses should be recruited for the current study. However, to reduce the chances of higher attrition due to the unpredictable nature of the hospital environment, the researchers decided to recruite 80 staff nurses.

$$n=\frac{{\left[Z_{1-\frac{\alpha }{2}}+Z_{1-\beta }\;\right]}^{2}\sigma^{2}}{d^{2}}$$

*n* = minimum sample size required

$Z_{1-\frac{\alpha }{2}}$
 = 1.96 at
*α* = 0.05

$Z_{1-\beta }$
 = 0.84 at 80% power

*σ* = population SD of the outcome variable = 12.3

*d* = clinically significant difference = 5

$$∴n=\frac{{\left(1.96+0.84\right)}^{2}{\left(12.3\right)}^{2}}{5^{2}}=50$$

With 20% drop out rate

$$n*=\frac{n}{1-0.3}\;=\frac{50}{0.2}=63\;\left(\text{approx}.\right)$$

As nurse-in-charges of all the general wards of the selected hospital will be approached for their consent to participate using complete enumeration, a sample size calculation was not performed. Similarly, a sample calculation was not performed for patients, because only those in-patients who will be receiving care from the recruited staff nurses will be approached for their consent to participate in the study.

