### Data collection

2.9

Data from the staff nurses, patients, and nurse-in-charges will be collected at baseline and 3-month pre-intervention, and immediately after the intervention, at 3-month, and 6-month follow-up by the investigator. Multiple baselines enable an assessment of whether changes occur after or during an intervention, rather than before or as a result of any extraneous factor (
Dundas, Binder, Hansen, & Stige, 2017). The questionnaires will be completed by the participants on the same day. The investigator will always be present with the participants when they fill in the questionnaire and will provide help to understand the questionnaire’s statements if needed. All the participants will be given a unique code to maintain confidentiality and to make sure that only the participants who have consented to participate complete the questionnaires. The investigator will collect the questionnaires on completion and store them safely in a folder. The investigator has considered an attrition rate of 20% while calculating the sample size, to account for participants who discontinue the intervention or follow-ups. Also, the investigator will maintain an attendance sheet of the participants. Reminders will be sent, and calls will be made to the study participants about upcoming and missed sessions.

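### Neither printed step of the sample size derivation gives its printed result; the stated figures need correcting, but the 80 recruited covers every version

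*Protocol article*

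**What the plan says.** Section 2.5 (Sample size and selection) gives its assumptions in one sentence: "At a 20% dropout rate, 80% power, SD of 12.3 (taken after feasibility study), and clinically significant difference of 5". From these it concludes that "it was calculated that approximately 63 staff nurses should be recruited for the current study".

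It then sets out the derivation. The formula is the normal-approximation one for a single mean, with 1.96 for two-sided α = 0.05, "0.84 at 80% power", "population SD of the outcome variable = 12.3" and "clinically significant difference = 5". The result is printed as 50. Under the label "With 20% drop out rate" the inflation step follows, which reads in its typeset source "n*=\frac{n}{1-0.3}\;=\frac{50}{0.2}=63", marked as approximate.

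The same section says that the researchers chose to recruit 80 nurses, as extra cover against attrition. Section 2.9 (Data collection) repeats the rate: "The investigator has considered an attrition rate of 20% while calculating the sample size".

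**The concern.** Both equals signs that matter look false. The first turns the stated inputs into 50, which they do not give. The second is a chain of three terms, no two of which are equal, and its denominators (0.7 and 0.2) do not match the 20% rate in the label above it.

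This is the only sample size calculation in the article; section 2.5 says that none was done for the patients or the nurses-in-charge. Other text leans on it. Section 2.9 cites it for the attrition allowance, and section 7 (Strengths and Limitations) says that the risk of higher attrition was dealt with at that stage. A derivation offered as that safeguard should be reproducible from what is printed. At stake is the correctness of the published figures, not whether enough nurses were recruited.

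**Working it through.** **Inputs, all from section 2.5:** z = 1.96 and z = 0.84; σ = 12.3; d = 5; dropout 20% (also in section 2.9); recruitment target 80. The values 12.3 and 5 are taken as given here.

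**Step 1, base n by the printed formula.**
- (1.96 + 0.84)² = 2.80² = 7.84
- 12.3² = 151.29
- 7.84 × 151.29 / 25 = 1186.11 / 25 = 47.44, rounded up to 48

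The printed value is 50. Unrounded z-values do not close the gap: they give 47.50, again 48.

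**Step 2, the dropout step as printed, from a base of 50.**
- First fraction: 50 / (1 − 0.3) = 50 / 0.7 = 71.4
- Second fraction: 50 / 0.2 = 250
- Printed result: 63

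**Step 3, recovering 63.** At the stated 20%, 50 / (1 − 0.2) = 50 / 0.8 = 62.5, about 63. So 63 is the right inflation of 50 at 20%, although that expression is not the one printed.

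**Step 4, each combination of base and loss.**

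| Base n | 20% loss | 30% loss |
|---|---|---|
| 48 (printed formula) | 48/0.8 = 60 | 48/0.7 = 68.6, so 69 |
| 50 (printed result) | 50/0.8 = 62.5, so 63 | 50/0.7 = 71.4, so 72 |

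The printed formula with the stated 20% therefore leads to 60, three fewer than the printed 63.

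**Step 5, the margin in the 80 recruited.**
- At 20% loss: 80 × 0.8 = 64 completers
- At 30% loss: 80 × 0.7 = 56 completers
- Loss that would leave exactly 50: 1 − 50/80 = 37.5%
- Loss that would leave exactly 48: 1 − 48/80 = 40%

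**Step 6, a possible source of 50.** A two-sided one-sample t calculation with SD 12.3 and difference 5 has power 78.8% at n = 48, 79.6% at 49 and 80.4% at 50, so it would require 50. The article neither shows nor mentions such a calculation.

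**The case against.** The strongest reply is that this is a typographical slip without consequence. Most of that stands. The 20% rate is given in words three times, twice in section 2.5 and once in section 2.9, while 30% appears only as a digit in one denominator. The 0.2 in the second fraction is most naturally the stated 20% set where 0.8 belongs, rather than another planned rate. The gap between 48 and 50 is two nurses and errs on the safe side. Section 9 (Study status) reports the intervention delivered and follow-up completed in May 2022, so no recruitment decision is open.

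Three stronger readings are tempting, and the documents do not support them:

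- **That the planned dropout rate is unknown, so the margin in 80 is unclear.** The words consistently say 20%, the printed 63 follows from 50 at 20% and not at 30%, and the margin can be computed at either rate.
- **That the study is too small.** The target of 80 exceeds all four totals in the table.
- **That 50 came from a paired t calculation.** The numbers agree, but section 2.5 prints only the normal formula and describes 12.3 as the population SD of the outcome, not the SD of paired differences. The agreement may be coincidence, and only the authors can say.

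What the reply does not remove is that the article chose to print the derivation, and both of its steps are wrong as printed. The full protocol or an analysis plan would not be expected to supply this, because the figures are already here.

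**Conclusion.** The point holds as a correction to the stated figures. The base formula gives 47.4, rounded up to 48, where 50 is printed. The dropout step equals neither 63 nor itself, and it conflicts with the 20% stated in words. The printed formula and the stated rate together give 60, not 63. The dropout terms are most likely misprints, since 50/0.8 gives the printed total; the origin of 50 remains unexplained.

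The size is small: two nurses at the base and three after inflation. Under the stated α, power, SD and difference, the 80 recruited leaves about 64 completers at 20% loss and 56 at 30%, both above 48 and 50. The adequacy of the sample under those assumptions is unaffected. This rests on taking 12.3 and 5 at face value.

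**What to change.** In section 2.5:

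1. Print the dropout step as n/(1 − 0.2), in line with the 20% given in sections 2.5 and 2.9.
2. Correct the base to 47.4, rounded up to 48, so that the total is 48/0.8 = 60, and change 63 to 60 in the opening sentence. If 50 came from another calculation, name that method and its inputs instead, and print 50/0.8 = 62.5, about 63.
3. Add one sentence saying that 80 recruits give about 64 completers at 20% loss.

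The cost is two equations, one added sentence and, in the first case, one changed figure in the text. Design, recruitment and analysis are unaffected.
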